### 2.9. Statistical Analysis

Statistical Package for the Social Sciences (SPSS) program version 23.0 will be used to analyse the data. The data will be presented as mean ± SD for parametric data and median (range) for non-parametric data. The normality of data distribution will be tested using the Shapiro–Wilk test. A *p*-value of <0.05 will be used to denote statistical significance. Descriptive analysis including frequencies, percentage, mean, and standard deviation will be used to analyse sociodemographic data and blood pressure.

For the effects of meal replacement on metabolic profiles, anthropometric measurements, satiety levels, hormonal changes, and QoL scores, mixed-design ANOVA will be used to compare between the intervention group and the control group to determine the interaction effect of intervention and time.

To determine the cost-effectiveness, incremental cost-effectiveness ratios (ICER) will be calculated by dividing the difference in total costs (between control and treatment) with the difference in the chosen measure of health outcome or effect (QALY). To assess the sustainability of the meal replacement, mixed-design ANOVA will be used to compare clinical parameters and hormonal level changes between groups on week 12 and week 48.

The main analysis will be conducted in the intention-to-treat (ITT) population in which missing values will be predicted by using the estimating equation method by adapting statistical models to the data observed using the missing-at-random method. Complete case analysis will also be performed in the per-protocol (PP) population.

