## Abstract

Meal replacement (MR) is widely used in weight and diabetes management programs due to its ease of compliance and handling. However, little is known about its impact on outcomes other than glycaemic control and weight loss. Furthermore, not many studies evaluate its cost-effectiveness and sustainability. This study aimed to evaluate the efficacy of a diabetes-specific MR for the weight reduction and glycaemic controls of overweight and obese T2DM patients, as compared to routine dietary consultation. Other health outcomes, the cost effectiveness, and the sustainability of the MR will also be evaluated. Materials and Methods: This randomised controlled clinical trial will involve 156 participants who have been randomised equally into the intervention and control groups. As a baseline, both groups will receive diet consultation. Additionally, the intervention group will receive an MR to replace one meal for 5 days a week. The duration of intervention will be 12 weeks, with 36 weeks of follow-up to monitor the sustainability of the MR. The primary endpoints are weight and Hemoglobin A1c (HbA1c) reduction, while the secondary endpoints are anthropometry, biochemical measurements, satiety, hormone changes, quality of life, and cost-effectiveness. The impact of the COVID-19 pandemic on study design is also discussed in this paper. This study has obtained human ethics approval from RECUKM (JEP-2019-566) and is registered at the Thai Clinical Trials Registry (TCTR ID: TCTR20210921004).

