#### 1.1.1. Primary Endpoint

Changes in HbA1c and bodyweight from the beginning of treatment to week 12 after initiation of treatment

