### 2.2. Sample Size

Sample size is calculated using G *Power 3.1 software. The protocol for calculation is as shown below in Table 2. We employed an effect size of 0.2055067, which is obtained from the mean difference value of the HbA1c (%) result in a study by Keogh and Clifton [18]. Based on the calculation, a total of 120 participants is needed for the study. In order to account for up to a 30% dropout, a total of 156 participants will be recruited for this study.

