## Figures and Tables

**Figure 1 ijerph-19-04188-f001:**
[figure not shown]
Research Flow Chart.

**Table 1 ijerph-19-04188-t001:** Inclusion and Exclusion Criteria.

Inclusion Criteria	Exclusion Criteria
Aged 20–65 years old	On insulin treatment
Diagnosed with T2DM for at least 6 months with baseline HbA1c levels between 7.5% and 12% for the past 3 months	With chronic kidney disease or on continuous ambulatory peritoneal dialysis or hemodialysis (GFR < 30 mL/min/1.73 m^2^)
Overweight or obese with BMI ≥ 25 kg/m^2^	With hepatic diseases (ALT > 120 IU/L)
On stable doses of any oral hypoglycaemic agents for the past 3 months	With history of chronic alcohol abuse
	Pregnant and lactating women
	Currently consuming any weight reduction products or any slimming prescriptions
	Currently involving in weight loss programs
	Record of COVID-19 diagnosis

**Table 2 ijerph-19-04188-t002:** Protocol for calculation in G*Power.

Sample Size Calculation	
F tests—ANOVA: Repeated measures, between factors	
Analysis: A priori: Compute required sample size	

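### Two unranked primary endpoints, each tested at an unadjusted 0.05, with no statement of whether success needs either or both

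*Protocol article*

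**What the plan says.** Section 1.1.1 of the protocol article gives the primary endpoint as "Changes in HbA1c and bodyweight from the beginning of treatment to week 12 after initiation of treatment". The Abstract agrees: "The primary endpoints are weight and Hemoglobin A1c (HbA1c) reduction". Neither place puts one endpoint ahead of the other.

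Section 2.9 fixes a single criterion for all analyses, a p-"value of <0.05 will be used to denote statistical significance". For metabolic and anthropometric outcomes, which include HbA1c and weight, it says that "mixed-design ANOVA will be used to compare between the intervention group and the control group to determine the interaction effect of intervention and time". It gives no testing order, no division of alpha and no rule for combining the two primary results.

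Section 2.2 sizes the trial on HbA1c alone. The effect size is "obtained from the mean difference value of the HbA1c (%) result" in an earlier study. Table 2 uses the whole alpha of 0.05, and no calculation for weight is given.

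**The concern.** With two primary endpoints and a flat 0.05 for each, nothing in the text stops a significant result on one of them from being reported as a positive primary result. Each endpoint then gives a separate chance of a false claim.

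A result that is significant for weight but not for HbA1c, or the reverse, also has no interpretation fixed in advance. Whether the trial met its primary objective could be settled after the data are seen. The trial is open-label (section 2.5) and has no external data monitoring board (section 2.11), so a rule fixed beforehand is worth more than usual.

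**Working it through.** **Inputs**
- Two primary endpoints: section 1.1.1.
- Alpha 0.05 per test: section 2.9 and Table 2.
- Effect size f = 0.2055067, 2 groups, 4 measurements, correlation 0.5 among repeated measures, N = 120: Table 2.
- Correlation between the HbA1c and weight test statistics: not given, so varied as an assumption.
- One test per endpoint: assumed.

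**1. Reproducing the plan's own figure.** Table 2 names the procedure as "F tests—ANOVA: Repeated measures, between factors". Its noncentrality parameter is

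λ = f² × N × m / (1 + (m − 1)ρ) = 0.2055067² × 120 × 4 / (1 + 3 × 0.5) = 8.1087.

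The critical F on 1 and 118 degrees of freedom at 0.05 is 3.9215, and power is 0.8063. All three match Table 2. So the stated N of 120 is the number for one endpoint at undivided alpha.

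**2. Either endpoint suffices.** With both null hypotheses true and the tests independent:

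1 − (1 − 0.05)² = 0.0975, with an upper bound of 0.05 + 0.05 = 0.10.

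For correlated tests, the error is 1 − P(|Z₁| < 1.96 and |Z₂| < 1.96) under a bivariate normal distribution:

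| Assumed correlation | Two-sided family-wise error |
|---|---|
| 0 | 9.75% |
| 0.3 | 9.5% |
| 0.5 | 9.1% |
| 0.7 | 8.4% |
| 0.9 | 7.0% |

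These count false claims in either direction. A false claim in favour of meal replacement has probability 1 − 0.975² = 4.9% at correlation 0 and 4.5% at 0.5, against 2.5% for a single endpoint.

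**3. Both endpoints required.** The error is at most 5%, because a false claim needs the test of a true null to be significant. If both nulls are true and the tests independent, it is 0.05² = 0.25%. The open question is power: the chance of winning on both cannot exceed the HbA1c power of 80.6%. As an illustration only, if weight also had 80.6% power and the tests were independent, joint power would be 0.8063² = 65%. The document gives no weight power, so the real figure cannot be derived.

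**4. Alpha divided equally.** At 0.025 per endpoint the error is 1 − 0.975² = 4.94% under independence. The step 1 formula at 0.025 gives 71.8% power at N = 120, and 80% needs N = 144 before dropout.

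**The case against.** Three points on the other side have force.

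- A rule for combining primary endpoints is often written in the statistical analysis plan, which is not shown, and a journal article condenses the full protocol. Silence alone would be no finding. Here, though, the article is not silent on error control: it fixes the endpoints, the threshold and the alpha used for sizing. What stands is that a rule may exist elsewhere; the published text applies an unadjusted threshold.
- A reader might infer that the plan carries an error of almost 10% as a fixed property. The documents do not support that. The figure needs either endpoint to suffice, both nulls to be true and near-independent tests. HbA1c and weight change are measured in the same patients, and correlation in either direction lowers the figure. The endpoints are joined by a plain *and*, which is not a decision rule but leaves a both-required reading open.
- A reader might also infer that sizing on HbA1c at full alpha rules out a both-required design. It does not. Requiring both uses exactly 0.05 per endpoint; only the joint power is unexamined. The same sizing also fits a hierarchy led by HbA1c. The sample size is therefore not evidence of uncontrolled error.

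The correlated figures are also approximate. They use normal test statistics, whereas section 2.9 plans group-by-time F tests over several visits.

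**Conclusion.** The concern holds as an ambiguity that should be closed. The error rate for the primary claim depends on a choice the protocol does not make: at most 5% if both endpoints are required, and up to about 10% two-sided if either is enough. For assumed correlations from 0.3 to 0.7 the latter is roughly 9.5% down to 8.4%. These figures rest on one test per endpoint and on both nulls being true; the correlations are assumptions. The power figures rest on the inputs in Table 2 taken as given. The stated 80% power supports a claim on HbA1c alone. It covers neither an equal split of alpha nor joint success.

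**What to change.** Add to section 2.9: the between-group comparison of change in HbA1c from baseline to week 12 is tested first at two-sided 0.05; the same comparison for bodyweight is tested at two-sided 0.05 only if HbA1c is significant; otherwise weight is reported as an estimate with a confidence interval and no confirmatory claim.

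This holds the family-wise error at 5%, leaves N and the HbA1c power unchanged, and gives split results a fixed reading. The downside is that weight cannot support a confirmatory claim if HbA1c fails, however strong the weight result. Section 3 reports that the intervention had not started at the time of writing, so the sentence could be added before outcome data exist.

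Alternatives, if the sponsor does not want that order:
- **Require both endpoints at 0.05 each.** No alpha adjustment is needed. Joint power is at most 80.6%, and a weight calculation should be added.
- **Holm over the two endpoints.** No order is imposed, but the first step is at 0.025, which gives about 72% power per endpoint at N = 120 on the stated inputs; 80% at that step needs 144 before dropout.

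If an unpublished analysis plan already contains a rule, stating it in section 2.9 is enough.

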### 2.5. Randomisation

Following the baseline measurement, participants will be randomised into the MR group and control group at a 1:1 ratio. A third-party statistician will carry out the randomisation using the Winpepi computer program with minimisation method [19]. Gender (men, women), HbA1c (≤8.5% or >8.5%), and BMI (≤25 or >25) at the time of baseline measurement will be balanced in each group. Treatment allocation will not be blinded to both researchers and participants due to the nature of the intervention. The participants will be informed about which group they should accordingly be in before the intervention process starts.

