### 2.8. Data Collection and Outcome Measurement

All participants are required to attend the clinic at baseline, 6th, 12th, 24th, 36th, and 48th week for data collection (Table 3).

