**Input**	
Effect size f	= 0.2055067
α err prob	= 0.05
Power (1-β err prob)	= 0.80
Number of groups	= 2
Number of measurements	= 4
Corr among rep measures	= 0.5

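### The test named for the primary outcomes is an unadjusted group-by-time interaction with no visits stated, so it is not tied to the week-12 endpoint and forgoes baseline adjustment

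*Protocol article*

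**What the plan says.** Section 1.1.1 of the protocol article defines the primary endpoint as "Changes in HbA1c and bodyweight from the beginning of treatment to week 12 after initiation of treatment".

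Section 2.9 gives a single inferential rule for metabolic profiles, anthropometry, satiety, hormones and quality of life: "mixed-design ANOVA will be used to compare between the intervention group and the control group to determine the interaction effect of intervention and time". Both primary outcomes fall under it. The section does not say which visits are the levels of time, names no contrast at week 12 and lists no covariates. It then adds a separate analysis for sustainability, in which "mixed-design ANOVA will be used to compare clinical parameters and hormonal level changes between groups on week 12 and week 48".

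On the schedule, section 2.8 states that "All participants are required to attend the clinic at baseline, 6th, 12th, 24th, 36th, and 48th week for data collection". Table 3 has weight at all six of these visits. HbA1c is taken at weeks 0, 12 and 48 only (Table 3 and section 2.8.7). Sections 2.6 and 2.6.3 mention only weeks 6, 12 and 48 after baseline.

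On allocation, section 2.5 states that "A third-party statistician will carry out the randomisation using the Winpepi computer program with minimisation method". The balancing factors are gender, HbA1c (cut at 8.5%) and BMI (cut at 25).

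**The concern.** A group-by-time interaction asks whether the two mean profiles differ in shape anywhere among the visits entered. The endpoint asks whether the groups differ in change at one visit. The two questions coincide only when the time factor has exactly two levels, baseline and week 12. With more levels, a significant result may come from later visits, and a real week-12 effect may be spread over several degrees of freedom and missed.

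The stated model also treats baseline as one more outcome level. Baseline is therefore subtracted, but not used as a predictor. The factors that steer allocation do not appear either. Where such a factor predicts outcome, as baseline HbA1c should predict week-12 HbA1c, the unadjusted standard error is larger than the true sampling variability under minimisation.

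At stake are whether the primary result answers the stated question, and how much power is given up.

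**Working it through.** **Inputs.** From section 2.2 and Table 2: f = 0.2055067 ("We employed an effect size of 0.2055067"), N = 120, 4 measurements, correlation ρ = 0.5, α = 0.05; 156 are to be recruited. For two equal groups d = 2f = 0.411. I assume unit SD at each visit and equal correlations, as Table 2's single ρ implies. The effect size comes from an HbA1c result, so using it for weight is an assumption.

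**Step 1: the plan's own figure.** Table 2 uses the between-factors test: λ = N·f²·m / (1 + (m−1)ρ) = 120 × 0.042233 × 4 / 2.5 = 8.1087 on 1 and 118 df, power 0.8063. This reproduces Table 2. It is the power for a group difference averaged over visits, so it describes neither the interaction nor a week-12 comparison.

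**Step 2: the interaction.** With group differences δ_j at the m visits, λ = (N/4)·Σ(δ_j − mean δ)² / (1 − ρ), on m−1 and (m−1)(N−2) df. Here (N/4)d² = 30 × 0.16893 = 5.068.

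| Visits entered | δ in units of d | Σ of squares (units of d²) | λ | df | Power |
|---|---|---|---|---|---|
| HbA1c 0/12 | 0, 1 | 0.500 | 5.07 | 1, 118 | 0.61 |
| HbA1c 0/12/48, effect kept | 0, 1, 1 | 0.667 | 6.76 | 2, 236 | 0.63 |
| HbA1c 0/12/48, effect at week 48 only | 0, 0, 1 | 0.667 | 6.76 | 2, 236 | 0.63 |
| HbA1c 0/12/48, half kept | 0, 1, ½ | 0.500 | 5.07 | 2, 236 | 0.50 |
| Weight 0/6/12 | 0, ½, 1 | 0.500 | 5.07 | 2, 236 | 0.50 |
| Weight, six visits, effect kept | 0, ½, 1, 1, 1, 1 | 0.875 | 8.87 | 5, 590 | 0.61 |
| Weight, six visits, effect wanes | 0, ½, 1, ½, ¼, 0 | 0.719 | 7.29 | 5, 590 | 0.51 |

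Rows 2 and 3 make the point. Over weeks 0/12/48 the test has the same power whether the effect is present from week 12 or is absent at week 12 and appears only at week 48. Rejection alone does not show which occurred.

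**Step 3: baseline adjustment at week 12.** The variance factor is 2(1 − ρ) for the change score and 1 − ρ² for ANCOVA; their ratio is (1 + ρ)/2. The change-score test equals the two-visit interaction. Values of ρ other than 0.5 are assumptions that show the range.

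| ρ | Variance ratio | λ change | λ ANCOVA | Power change, N = 120 | Power ANCOVA, N = 120 |
|---|---|---|---|---|---|
| 0.3 | 0.65 | 3.62 | 5.57 | 0.47 | 0.65 |
| 0.5 | 0.75 | 5.07 | 6.76 | 0.61 | 0.73 |
| 0.7 | 0.85 | 8.45 | 9.94 | 0.82 | 0.88 |
| 0.8 | 0.90 | 12.67 | 14.08 | 0.94 | 0.96 |

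At ρ = 0.5, power goes from 0.72 to 0.84 with all 156 analysed, and from 0.57 to 0.69 with 109 (156 × 0.7 = 109.2, the 30% dropout that the plan allows for). The total for 80% power falls from 188 to 142.

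**Step 4: minimisation.** I simulated 4,000 null trials per setting with N = 120, minimising on sex, HbA1c cut at its mean (8.5% is the mean in Table 4) and BMI. Assumed: an 80% biased coin, 60% men, 95% above the BMI cut, sex and BMI not prognostic. At ρ = 0.5 the unadjusted change-score test rejected 3.4% at nominal 5% (average model SE 0.182 against a true 0.168). ANCOVA rejected 5.3% (0.158 against 0.159). At ρ = 0.7 the rates were 4.3% and 5.7%. The Monte Carlo standard error is about √(0.05 × 0.95/4000) = 0.34 percentage points.

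**The case against.** A reader might infer that the primary test misses week 12 for both endpoints. The article does not support that. Because weeks 12 and 48 have their own sustainability analysis, the general ANOVA may well be meant for the intervention period. For HbA1c, the outcome on which the trial is sized, this leaves weeks 0 and 12. The interaction is then a 1-df change-score test that isolates the endpoint. This stands for HbA1c. It does not rescue weight, where weeks 0/6/12 still give 2 df.

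It is also tempting to read the waning six-visit case (0.51) as the cost of the plan. It rests on an assumed course and a borrowed effect size. If the effect is kept to week 48 the same test has 0.61, no worse than a change score, and the three-visit HbA1c test has 0.63 in that case. Most of the dependable loss comes from the missing baseline adjustment, and that shrinks as ρ rises. Table 2's 0.5 is a planning input; nothing shows that it was estimated.

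The article is condensed and does not exclude covariates; an analysis plan could name them. That is fair, and silence alone would not be a finding. But section 2.9 does name a test for the primary outcomes, and as written that test is loosely matched to the endpoint.

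Finally, entry requires BMI of at least 25, so a BMI factor cut at 25 separates almost nobody and its omission as a category costs almost nothing.

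**Conclusion.** The concern holds in a limited form. Section 2.9 names an unadjusted interaction test and leaves its visits open, while the endpoint is fixed at week 12. Whether the HbA1c test isolates week 12 depends on which visits enter; the weight test does not isolate it on any reading of the schedule. On every reading the stated model omits a baseline covariate and the minimisation factors. Against a week-12 change score, adjustment adds about 12 percentage points of power at N = 120 under the plan's ρ of 0.5. Over ρ from 0.3 to 0.8 the gain runs from about 18 points down to about 2.

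A reader might infer a risk of false positives from ignoring the minimisation factors. The direction is the opposite: standard errors are somewhat too large and the test is conservative.

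The power figures rest on the HbA1c effect size, equal correlations and, for weight, half the effect being present at week 6. Severity: should-fix.

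**What to change.** In section 2.9, state that each primary endpoint is analysed as the week-12 difference between groups with a 95% confidence interval. Obtain it from a linear mixed model of the post-baseline values with group, visit and group-by-visit, taking the week-12 contrast, or from a week-12 ANCOVA. Adjust for the continuous baseline value of that outcome, gender, continuous baseline HbA1c (entered once in the HbA1c model, where it is also the outcome's baseline) and continuous baseline BMI. List the visits that enter each model. Keep the overall interaction as supportive, and leave the week-12 and week-48 comparison as the sustainability analysis.

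The cost is a few sentences. All covariates are already collected at baseline and SPSS, already named, can fit these models. Section 3 reports that the intervention had not begun when the article was written. The change should be dated and made before any outcome data are examined by group.

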#### 2.8.10. Cost-Effectiveness

Quality-adjusted life years (QALY) will be the main outcome parameter for the evaluation of cost-effectiveness from a societal perspective. EuroQol five-dimension Inventory (EQ-5D-5L) will be utilised in this study to calculate QALY. It is the most used instrument worldwide in economic evaluations that measure health benefits in terms of QALY [43]. English and Malay versions of EQ-5D-5L, which have been validated for use in the Malaysian population, will be utilised in this study [44,45].

EQ-5D-5L is a self-report questionnaire that assesses five life domains, including mobility, self-care, usual activities, pain/discomfort, and anxiety/depression [43]. There is also an EQ-VAS section to measure respondents’ perception of their overall current health on a vertical visual analogue scale with ‘100′ corresponding to ‘The best health you can imagine’ and ‘0′ representing ‘The worst health you can imagine’.

Scores on the five dimensions will be totalled up and converted into utility weights for computing QALY using the EQ-5D algorithm. Analysis will be conducted to estimate the direct and indirect costs for the intervention group and the control group for routine diabetes care. Intervention costs will then be estimated by using a bottom-up micro-costing analysis that will include meal replacement cost and operational costs such as dietician’s salary. The cost for control group or routine diabetes care will be estimated from a questionnaire on participant’s health care utilisation (general practitioner, dietician, physiotherapist, consultations at outpatient clinic, and hospitalisation) and use of medication.

The cost per QALY gained will be computed, and incremental cost-effectiveness ratios (ICER) will be calculated as the difference in costs divided by the difference in QALYs between the intervention and the control group using a bootstrap analysis. A cost-effectiveness plane can be plotted to indicate which intervention is more effective or expensive than the other.

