## 4. Discussion

The global epidemic of obesity and associated T2DM direly needs a greater emphasis on effective lifestyle intervention programs for patients. Meal replacement is often included as a part of the lifestyle intervention program as it is effective as an initial phase for diabetic patients to lose weight in a therapeutic program [46]. Previous trials utilising meal replacements on obese or T2DM patients have demonstrated significant improvements in HbA1c, weight, lipid profile, insulin sensitivity, and cardiovascular risk factors [47,48,49,50,51].

This prospective, randomised, controlled open-label trial will focus on evaluating the effectiveness of a diabetes-specific meal replacement formulation on the weight loss and glycemic control of obese and overweight T2DM patients. To date, this is the first trial of its kind to test the efficacy of this low glycemic indexed meal replacement formulation containing cinnamon extract (*Cinnulin MS*) on overweight or obese T2DM patients. There is also a lack of studies on short-term meal replacement intervention in a sufficiently powered and well-designed clinical trial in Malaysia. We hypothesised that the meal replacement intervention would be effective in maintaining weight loss, improving glycaemic control parameters, and improving the quality of life of the participants.

Apart from anthropometry and biochemical analysis, a cost-effectiveness analysis of the meal replacement intervention will also be conducted, in comparison with the standard care in public. It is anticipated that this meal replacement intervention in T2DM management would be more cost-effective, as simulated in the other study (Stephen 2010).

Meal replacements have been proven to improve patients’ weight and glycaemic control. However, due to the lack of further intervention following the completion of the initial intervention, it has also been shown to be less effective in maintaining glycaemic control in some meal replacement studies. This is shown in a study by Ash et al., in which the HbA1c levels of the participants who received a 12-week diet intervention with meal replacement returned to baseline levels after their 18th month follow-up [16]. Similar results of weight and HbA1c levels rebounding have been reported in other studies [52,53,54].

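### Cost-effectiveness rests on a bootstrapped ICER, which cannot be interpreted alone if the QALY difference is small; summarise the paired bootstrap as differences, quadrant shares and net benefit

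*Protocol article*

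**What the plan says.** Cost-effectiveness is part of the research objective (section 1.1) and one of the secondary endpoints (section 1.1.2 and the Abstract). Section 2.8.10 fixes the effect measure: "Quality-adjusted life years (QALY) will be the main outcome parameter for the evaluation of cost-effectiveness from a societal perspective". QALYs come from the EQ-5D-5L, which Table 3 schedules at weeks 0, 12, 24, 36 and 48.

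The result is defined twice. Section 2.8.10 describes the ICER "as the difference in costs divided by the difference in QALYs between the intervention and the control group using a bootstrap analysis". Section 2.9 introduces the ICER as the way cost-effectiveness will be established, and writes that "incremental cost-effectiveness ratios (ICER) will be calculated by dividing the difference in total costs (between control and treatment) with the difference in" the health outcome, with QALY in brackets. It does not repeat the bootstrap.

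The plane is permitted but not required: "A cost-effectiveness plane can be plotted to indicate which intervention is more effective or expensive than the other". The article does not say which quantity the bootstrap will summarise (the ratio, the two differences, or a net benefit). The Discussion states an expectation: "It is anticipated that this meal replacement intervention in T2DM management would be more cost-effective".

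**The concern.** A ratio of two differences does not put results in order. A negative ICER arises when the product is cheaper and better and also when it is dearer and worse. A positive ICER arises when it is dearer and better and also when it is cheaper and worse, and these call for opposite decisions at most thresholds. As the QALY difference passes through zero, the ratio jumps between very large positive and very large negative values.

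This does little harm when the QALY difference is clearly away from zero. It matters when the difference is small relative to its standard error, because bootstrap replicates then fall on both sides of zero. A median or percentile interval of the replicate ratios would mix results with opposite meanings. The bootstrap is the only expression of uncertainty that the article names for this endpoint. If it is summarised on the ratio scale, the reader may get no usable statement of uncertainty.

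**Working it through.** **1. What the trial was sized for.** The article gives no figure for the cost-effectiveness analysis. Its sample size (section 2.2, Table 2) uses f = 0.2055067 from an HbA1c difference, with 4 measurements, correlation 0.5, α = 0.05 and power 0.80. With λ = f²·N·m / [1 + (m − 1)ρ]:

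- N = 120: λ = 0.042233 × 120 × 4 / 2.5 = 8.1087, critical F(1, 118) = 3.9215, power 0.8063. This matches Table 2.
- N = 118: power 0.7996.

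The number is reproduced, but it is an HbA1c number and gives no assurance about precision for QALYs.

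**2. Precision of the QALY difference.** With 1:1 allocation (section 2.5), SE = SD × √(4/N). The per-patient QALY SD over 48 weeks is not in the documents and is assumed here. At N = 156 (section 2.2), √(4/156) = 0.1601.

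| Assumed QALY SD | SE at N = 156 |
|---|---|
| 0.08 | 0.0128 |
| 0.12 | 0.0192 |
| 0.16 | 0.0256 |

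If 30% dropped out, about 109 would remain (156 × 0.70 = 109.2). The same formula then gives 0.0153 to 0.0307 across these SDs, before any gain from modelling the missing values.

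**3. How often the replicates straddle zero.** Call a trial straddling if more than 2.5% of replicates lie on each side of zero QALYs. By normal approximation, P(straddle) = Φ(1.96 − δ/SE) − Φ(−1.96 − δ/SE), where δ is the true QALY gain (also assumed). A simulation with 78 per arm, 1,500 trials and 1,000 paired resamples gives a comparison.

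| True gain δ | Normal approximation, SD 0.08 to 0.16 | Simulation |
|---|---|---|
| 0 | 0.95 | about 0.95 |
| 0.01 | 0.88 to 0.93 | 0.88 to 0.92 |
| 0.02 | 0.65 to 0.88 | 0.64 to 0.85 |

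A separate check under no effect, with 60 and 78 per arm and SD 0.05 to 0.20, found straddling in about 94 to 95% of trials.

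**4. Why a ratio summary then fails.** Illustrative units, differences as MR minus control. Net benefit = threshold × QALY difference − cost difference, at a threshold of 20,000.

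| Cost difference | QALY difference | ICER | Net benefit |
|---|---|---|---|
| +500 | −0.01 | −50,000 | 20,000 × (−0.01) − 500 = −700 (dominated) |
| −500 | +0.01 | −50,000 | 20,000 × 0.01 + 500 = +700 (dominant) |
| +500 | +0.01 | 50,000 | 200 − 500 = −300 |
| −500 | −0.01 | 50,000 | −200 + 500 = +300 |

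Each pair shares a ratio and has net benefits of opposite sign. Replicates from these four positions cannot be placed on one ICER scale and given a meaningful percentile interval. Net benefit has no such break: in the simulation of step 3, with an assumed cost difference of 1 unit and SD 1, its percentile interval covered the true value in 94 to 95% of trials.

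**5. Direction of subtraction.** Section 2.8.10 applies one phrase, intervention and control, to both differences. Section 2.9 names the cost difference in the other order. Either order used throughout gives the same ICER. Only a numerator in one order over a denominator in the other would reverse the sign.

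**The case against.** The strongest reply is that the article does not plan the faulty summary. It names a bootstrap, so the ICER is not left without uncertainty. It provides for a plane, which separates the quadrants and removes the shared-ratio problem wherever it is drawn. Both differences have to be computed to form the ratio, so their signs will be known. No percentile interval for the ICER is stated. A willingness-to-pay value, an acceptability curve and a decision rule are commonly left to a fuller plan, and their absence from an article is not an error. The passages on subtraction order are ordinary prose, not signed formulas. The Discussion's expectation is not a decision rule.

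Most of this stands. A reader might infer that the product would be called more effective half the time under no effect. The point estimate does favour it in 49 to 50% of simulated null trials, but that is true of any unbiased estimate, and the text does not say a verdict is read from it. Read as a 95% interval for the QALY difference, the bootstrap lies wholly above zero in only 2.5 to 3.2% of null trials. A reader might also infer that a bare ratio would look favourable in 72 to 85% of null trials. That figure requires every negative ratio to count as favourable, a fixed positive cost difference, and a cost assumed equal to 0.01 QALY at the threshold; none of these is in the documents.

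The reply does not remove the core point. The article makes the ratio the result and attaches the bootstrap to the ratio. The 2.5 to 3.2% comes from an interval for the QALY difference, which the article does not state, and the plane that would help is optional.

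**Conclusion.** The concern holds in a limited form. The measure chosen to carry the cost-effectiveness conclusion is poorly suited to a trial of this size, and the safeguard is optional. With an assumed QALY SD of 0.08 to 0.16, the SE is 0.013 to 0.026 at N = 156. Replicates would straddle zero QALYs in roughly 64 to 95% of trials for true gains from 0.02 down to 0. In those trials a summary of the ratio alone cannot be interpreted.

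The size depends on the assumed SD and gain, since the documents give neither; a larger gain or a smaller SD would reduce it. No rate of false claims of cost-effectiveness can be derived from the documents. The missing threshold is not in itself a fault, and the order of subtraction is a clarity point. This is a worthwhile improvement to a secondary endpoint and does not touch the primary analysis.

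**What to change.** In sections 2.8.10 and 2.9:

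- Resample patients within arm, keeping each patient's cost and QALY together.
- Report the cost difference and the QALY difference, each with a bootstrap interval.
- Make the plane mandatory and report the share of replicates in each quadrant.
- Report incremental net monetary benefit (threshold × QALY difference − cost difference) with a bootstrap 95% CI over a pre-stated range of willingness-to-pay values.
- Keep the ICER as a descriptive point value, with no percentile interval when replicates straddle zero QALYs.
- Define both differences as MR minus control in both sections.
- Adjust the QALY difference for baseline EQ-5D-5L utility, which Table 3 already collects at week 0, so that chance imbalance at baseline is not counted as a QALY effect.

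The cost is wording in two sections and a few lines of analysis code, with no new data or participants. The downside is that a threshold range must be named in advance and the conclusion may be less favourable to the product.
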